## Abstract

**Background:**

Septic shock, a critical condition characterized by organ failure, presents a substantial mortality risk in intensive care units (ICUs), with the 28-day mortality rate possibly reaching 40%. Conventional management of septic shock typically involves the administration of antibiotics, supportive care for organ dysfunction, and, if necessary, surgical intervention to address the source of infection. In recent decades, extracorporeal blood purification therapies (EBPT) have emerged as potential interventions aimed at modulating the inflammatory response and restoring homeostasis in patients with sepsis. Likewise, sequential extracorporeal therapy in sepsis (SETS) interventions offer comprehensive organ support in the setting of multiple organ dysfunction syndrome (MODS). The EROICASS study will assess and describe the utilization of EBPT in patients with septic shock. Additionally, we will evaluate the potential association between EBPT treatment utilization and 90-day mortality in septic shock cases in Italy.

**Methods:**

The EROICASS study is a national, non-interventional, multicenter observational prospective cohort study. All consecutive patients with septic shock at participating centers will be prospectively enrolled, with data collection extending from intensive care unit (ICU) admission to hospital discharge. Variables including patient demographics, clinical parameters, EBPT/SETS utilization, and outcomes will be recorded using a web-based data capture system. Statistical analyses will encompass descriptive statistics, hypothesis testing, multivariable regression models, and survival analysis to elucidate the associations between EBPT/SETS utilization and patient outcomes.

**Conclusions:**

The EROICASS study provides valuable insights into the utilization and outcomes of EBPT and SETS in septic shock management. Through analysis of usage patterns and clinical data, this study aims to guide treatment decisions and enhance patient care. The implications of these findings may impact clinical guidelines, potentially improving survival rates and patient outcomes in septic shock cases.

## Background

Septic shock, a critical condition characterized by organ failure, presents a substantial mortality risk in intensive care units (ICUs), with the 28-day mortality rate possibly reaching 40% [1]. The conventional management of septic shock typically entails antibiotics, supportive organ care, and surgical interventions as needed. In recent decades, researchers have explored extracorporeal blood purification therapies (EBPT) as supplementary treatments for immunomodulation during septic shock, including methods like high-volume hemofiltration (HVHF), the use of high cut-off (HCO) membranes, adsorption techniques, and plasmapheresis [2]. However, the clinical effectiveness of these EBPT technologies remains a topic of debate, necessitating verification through multicenter randomized controlled trials (RCTs). Septic shock frequently leads to acute kidney injury (AKI), impacting a significant portion of patients afflicted by this condition [3, 4]. Critically ill patients with sepsis-associated AKI who require renal replacement therapy (RRT) face an increased risk of mortality [3, 5, 6]. A novel approach, sequential extracorporeal therapy in sepsis (SETS) [7–9], has been proposed for multiple organ dysfunction syndrome (MODS) arising from endotoxic or septic shock. SETS envisions extracorporeal therapies serving as broad-spectrum support, sequentially replacing or supporting the function of multiple organs such as the heart, kidneys, liver, and lungs. Despite numerous studies, decisions about initiating EBPT or RRT in septic shock patients often rely on local clinical practices and the attending physician’s judgment. The optimal timing, modality, duration, and anticoagulation strategies for these therapies remain unclear. Particularly, in the Italian context, there remains a notable scarcity of high-quality data regarding the utilization of RRT and EBPT. Given this deficiency, this study aims to examine and describe the utilization of EBPT in septic shock patients, investigating any potential association between EBPT utilization and 90-day mortality. The study will also offer insights into EBPT utilization based on the presence of AKI in the context of septic shock in Italy.

### Study aim

The EROICASS study will assess and describe the utilization of EBPT in patients with septic shock. Additionally, we will evaluate the potential association between EBPT treatment utilization and 90-day mortality in septic shock cases in Italy.

## Methods

### Design

The EROICASS study is a national, nonprofit, non-interventional, multicenter observational prospective cohort study. The EROICASS study is co-sponsored by Anesthesia and Intensive Care at Santa Chiara Regional Hospital, APSS Trento, Trento, and the Società Italiana di Anestesia Analgesia Rianimazione e Terapia Intensiva (SIAARTI). The steering committee will grant authorship based on personal involvement, following the Vancouver definitions [10]. A group authorship (“SIAARTI study group”) will be established, encompassing all investigators from the participating centers, in accordance with predefined rules for authorship. The study adheres strictly to the principles outlined in the Helsinki Declaration and complies with all relevant local regulations governing patient ethics and consent. Moreover, the study design and reporting will adhere to the Strengthening the Reporting of Observational Studies in Epidemiology (STROBE) checklist to ensure transparency and completeness in reporting our findings.

### Setting

All consecutive patients with septic shock at the participating centers will be prospectively enrolled. Patient enrollment will coincide with ICU admission, and monitoring along with data recording will continue until hospital discharge. This study is observational in nature; enrolled patients will not receive additional treatments beyond those routinely administered in the ICU. All clinical parameters, including those associated with EBPT treatment, will be documented in the web-based CRF.

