##### Secondary outcome

To assess association between EBPT and 28-day and 90-day mortality in patients with septic shock.To assess the proportion of EBPT utilization in septic patients, according to the presence/absence of AKI.To describe indication, modality, and duration of EBPT in septic patients, also according to the presence/absence of AKI.\To assess proportion, indication, modality, and duration of SETS in septic patients with renal failure.To assess association between SETS utilization and 90-day mortality in septic patients with renal failure.To describe changes in blood lactate, vasoactive inotropic score (VIS), Sequential Organ Failure Assessment (SOFA) score, and AKI staged (with KDIGO criteria) before and after starting EBPT and SETS.To evaluate relationship between 90-day mortality and changes in blood lactate, VIS, SOFA score, and AKI staged (with KDIGO criteria) in patients undergoing EBPT and SETS.To evaluate relationship between fluid accumulation at EBPT initiation and 90-day mortality.To assess the frailty score change at 28- and 90-day post-discharge.To identify possible risk factors (e.g., baseline clinical parameters, features of EBPT) for 90-day mortality in patients with EBPT or SETS.To investigate the impact of time of EBPT and SETS on renal outcomes, mortality, ICU and hospital length of stay, and 28-day free EBPT (free-SETS days).

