### Timeline

The study recruits all consecutive patients with septic shock at the participating centers who will be prospectively enrolled (Fig. 1). Patient enrollment will coincide with ICU admission, and monitoring along with data recording will continue until hospital discharge will be prospectively enrolled. The study duration will be 12 months from the first IRB approval. Prior to the initiation of the study in September 2024, we anticipate that a minimum of 30 centers will be prepared for inclusion. It is noteworthy that the study is scheduled to commence before securing the majority of Institutional Review Board (IRB) approvals.

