### Data management

#### Data collection

Variables will be recorded upon ICU admission and monitored over 72 h, extending to ICU and hospital discharge. The following codified data will be collected via a collection form:Date, time of ICU admission, and originDemographic data and comorbiditiesAPACHE II score, SAPS II score, and SOFA scoreHemodynamic and perfusion parametersUse of vasopressorsConsciousness assessment (Glasgow Coma Score)Blood chemistry tests (platelet count, bilirubin levels, creatinine levels, azotaemia, potassium, sodium, urine quantity)Renal function and definition of renal damage according to KDIGO criteriaTiming, type, and duration of EBPTTiming, type, and duration of SETSVital status during ICU and hospital stayLong-term outcome post-discharge from ICU

The data will be generated and recorded in participating centers via a web application hosted by SIAARTI using REDCap® software. REDCap provides secure, web-based data capture tools with features including the following:Intuitive interface for validated data captureAudit trails for tracking data manipulation and export proceduresAutomated export procedures for data downloads to statistical packagesData integration and interoperability with external sourcesData will be recorded in the e-CRF using coding procedures to comply with data protection laws, including EU GDPR. Each patient will be assigned a unique subject ID for pseudonymized data analysis.

Access to REDCap will be granted only to data collecting staff of participating centers, adhering to outlined procedures. Unauthorized access is prevented through hierarchical, role-based access concepts. Data management and retention will be overseen by SIAARTI, ensuring secure storage accessible only to system administrators. Each participating center will have access only to the patient data it generated and recorded on the REDCap platform. Periodic ad hoc reports on collected data will be provided by each participating center. Measures for de facto anonymization will be established during data collection and processing, eliminating the need for name-related patient identification.

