### Statistical analysis plan

All parameters will be described by frequencies (absolute and relative) and mean (SD) or median (IQR) based on data distribution. EBPT and SETS will be described in terms of indication, modality, and timing. Differences between patients undergoing and not undergoing EBPT will be assessed using the chi-square test (for discrete variables) or Student’s *T*-test (for continuous variables). Continuous variables not normally distributed will be compared using appropriate nonparametric tests (such as Wilcoxon’s sign test). Similar tests will be conducted to compare patients alive at discharge (from ICU and from hospital) versus those who did not survive, as well as patients with and without AKI (according to KDIGO criteria).

For patients undergoing EBPT or SETS, paired tests (paired *t*-test, Wilcoxon signed-rank test) will be applied to assess statistical differences in lactates, VIS, SOFA score, and AKI stage (based on KDIGO criteria) before and after EBPT or SETS. Multivariable generalized linear regression models will be performed to investigate the association between clinical outcomes (renal outcomes, mortality, ICU and hospital length of stay, free days from EBPT or SETS) and demographic/clinical variables in patients undergoing EBPT or SETS. Depending on the number of participating centers, the characteristics of the centers collected in the case report form may be included in the list of predictor variables for the models.

Relationships will also be analyzed using survival analysis (Kaplan–Meier approach and Cox proportional hazard models) to account for failure time and censoring data. EBPT utilization will be reported in terms of absolute risk and 95% confidence levels. Absolute risk will also be estimated for patients with and without AKI. Estimates will be used to assess the risk ratio for mortality (at 28 days and 90 days) in the entire population and stratified according to the presence or absence of AKI. The same approach will be used to assess SETS utilization in the ICU. All hypothesis tests will be two-sided, and *P* < 0.05 will be considered to indicate statistical significance.

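### The protocol ends data recording at hospital discharge but needs 28-day and 90-day mortality, and its sections do not agree on when follow-up stops

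*Protocol article*

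**What the plan says.** Four places in the protocol article put the end of recording at hospital discharge:

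- Abstract, Methods: "with data collection extending from intensive care unit (ICU) admission to hospital discharge".
- Setting: "monitoring along with data recording will continue until hospital discharge".
- Timeline: the same rule again, in a garbled sentence, "monitoring along with data recording will continue until hospital discharge will be prospectively enrolled".
- Data collection: "Variables will be recorded upon ICU admission and monitored over 72 h, extending to ICU and hospital discharge". The only item in the list that names vital status covers the time in the ICU and in hospital.

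Other places need information beyond that point:

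- Study aim: "we will evaluate the potential association between EBPT treatment utilization and 90-day mortality in septic shock cases in Italy".
- Secondary outcome: "To assess association between EBPT and 28-day and 90-day mortality in patients with septic shock". Further objectives there use 90-day mortality for SETS, for changes in lactate, VIS, SOFA and AKI stage, for fluid accumulation, and for risk factors.
- Statistical analysis plan section: mortality risk ratios at 28 and 90 days, and survival analysis ("Kaplan–Meier approach and Cox proportional hazard models) to account for failure time and censoring data").

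Two places imply contact after discharge. One secondary outcome is "To assess the frailty score change at 28- and 90-day post-discharge". The Data collection list also has a long-term outcome after leaving the ICU, with no day and no stated content.

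**The concern.** A centre that follows Setting and Timeline would close the record when the patient leaves hospital. A centre that follows the frailty objective or the long-term outcome item would make a later contact. Whether a discharged patient has a day-90 status could then depend on which section the centre followed.

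The statistical stake is in the patients discharged alive before day 90. Without a later status, the analyst has two obvious choices. Counting them as survivors misses every death after discharge. Censoring them at discharge treats them as if they had the same future risk as patients still in hospital, which is implausible because patients are discharged when they are better. If length of stay or post-discharge mortality differs between patients with and without EBPT, either choice can distort the EBPT-mortality comparison, which is the one aim beyond describing use.

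**Working it through.** **The plan's own figure.** The only computed figures are the sample sizes. With p = 0.5 and 95% confidence, n = 1.96² × 0.25 / d². For d = 0.10 this is 96.04, rounded up to 97. For d = 0.05 it is 384.15, rounded up to 385. Both match the Sample size section. They rest on the EBPT proportion alone, so the end of follow-up does not change them. The article gives no figure for the mortality aim.

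**Sections side by side.** Take a patient discharged alive on day 20. Under Setting, Timeline and the abstract, recording stops on day 20. The risk ratios need the patient's status on days 28 and 90. The frailty assessments would fall 28 and 90 days after discharge, on days 20 + 28 = 48 and 20 + 90 = 110. The second would settle the day-90 status if the date of any death were recorded, but it is described as a frailty assessment and lies outside the stated recording period.

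**Illustration.** None of these inputs is in the documents, except that 40% echoes the Background section's upper figure for 28-day mortality:

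- 40% die in hospital, with exponential time to death, mean 9 or 6 days;
- survivors' hospital stay is lognormal, median 20 or 30 days, sigma 0.6;
- 8% of those discharged alive die by day 90 (varied from 5% to 12%).

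True 90-day mortality is about 0.40 + 0.60 × 0.08 = 44.8%.

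*Counting discharged patients as survivors* gives 40%. The undercount is 0.60 × q: 3.0 points at q = 5%, 4.8 at 8%, 7.2 at 12%.

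*Kaplan-Meier censored at discharge*, from 400,000 simulated patients per scenario:

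| Mean time to in-hospital death | Median stay 20 days | Median stay 30 days |
|---|---|---|
| 9 days | 56% | 46% |
| 6 days | 45.5% | 41.7% |

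Against a true value of about 45%, the error runs from about 11 points too high to 3 points too low. It also depends on the spread of stay: with a 9-day mean and 20-day median stay, sigma 0.8 gives 52% and sigma 0.4 gives 87%.

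**Effect on the comparison.**

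- Censoring, with no true difference but a median stay of 30 days with EBPT and 20 without: 0.46/0.56, about 0.81 with the 9-day mean; 41.7/45.5 = 0.92 with the 6-day mean.
- In-hospital counting, 40% in-hospital death and equal post-discharge risk in both groups: ratio 1.00, no bias.
- In-hospital counting, 40% in-hospital death in both groups, post-discharge death 15% versus 5%: true ratio (0.40 + 0.60 × 0.15)/(0.40 + 0.60 × 0.05) = 0.49/0.43 = 1.14, observed 1.00.
- In-hospital counting, in-hospital death 50% versus 40%, post-discharge death 10% in both: true ratio 0.55/0.46 = 1.20, observed 1.25.

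**Day 28.** With the 9-day mean and 20-day median stay, true mortality is about 39%. In-hospital counting gives 38%, and Kaplan-Meier censored at discharge gives 45%. With a 10-day mean and 30-day median stay, the censored estimate is 40% against a true 38%. Counting is therefore at most about 1 point low, and the largest censoring error here is about 6 points, against 11 at day 90.

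**The case against.** A reader might infer that patients discharged alive have no day-90 status at all, and that the 28- and 90-day results are therefore biased. The documents do not support that. The collection list has a long-term outcome item separate from in-hospital vital status, and the frailty objective needs contact after discharge. A natural reading is bedside monitoring to discharge plus a later outcome contact. The article nowhere says that live discharge is a censoring event or that discharged patients count as survivors. Detailed censoring rules and contact procedures are commonly left to the full protocol or analysis plan, and their absence from a condensed article is not an error.

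A reader might also infer that censoring at discharge always overstates mortality. The 6-day scenario with a 30-day median stay shows the opposite, and the assumed 10-day difference in stay between groups has no basis in the documents. Finally, mortality is an additional aim and a secondary outcome.

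All of this stands, and it limits the point. It does not remove the contradiction: the article does not leave the end of recording open but states it four times, and its own outcomes cannot be met under that statement. The long-term item has no day and starts at ICU discharge. The frailty assessments run on a clock from discharge, not from ICU admission.

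**Conclusion.** The contradiction holds and rests on the text alone. The consequence is conditional: if recording stops at discharge as written, patients discharged alive before day 90 lack a day-90 status. Counting them as survivors would then understate 90-day mortality by about 3 to 7 points if 5% to 12% of them die by day 90. Censoring them at discharge could move the Kaplan-Meier estimate in either direction, to between 42% and 56% against a true 45% in the four tabulated scenarios. A Cox model with the same censoring would describe the hazard of death in hospital, not mortality to day 90. The sizes and the direction rest on assumptions outside the documents and should not be read as predictions. The largest errors are smaller at day 28, and there is no effect on the EBPT proportion or on the 97 and 385 patients. This should be fixed before data collection, because a status that was not collected may be hard to recover later from pseudonymized records.

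**What to change.** Reconcile the abstract, Setting, Timeline and Data collection sections with the Study aim, Secondary outcome and Statistical analysis plan sections:

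1. Clinical data are recorded to hospital discharge.
2. Vital status, with date of death or of last contact, is recorded at day 28 and day 90 from ICU admission for every enrolled patient, wherever the patient then is. Name the source.
3. Live discharge or transfer is not a censoring event for mortality. Censor only at the last date known alive or at day 90.
4. Give the long-term outcome item a content and a day, and state that the frailty assessments lie within the recording period.

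The cost is protocol wording, a status and a date field if the form does not already have them, and one vital-status check per discharged patient. That check can share the contact already implied by the frailty objective. The sample size does not change. The calendar needs a look: 120 days of enrolment plus 90 days of follow-up is 210 days per centre, so the 12-month study covers day 90 for all patients only at centres approved within about 365 − 210 = 155 days of the first IRB approval. The frailty assessment at 90 days post-discharge ends later still.

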#### Study population

##### Inclusion criteria

Septic shock at ICU admission according to sepsis-3 guidelines11Age ≥ 18 years

##### Exclusion criteria

Lack of consentLife expectancy at the time of implementation less than 24 hNeed for extracorporeal membrane oxygenation (ECMO)

#### Outcome measured

##### Primary outcome

Primary outcome is to assess the proportion of EBPT utilization in septic patients.

##### Secondary outcome

To assess association between EBPT and 28-day and 90-day mortality in patients with septic shock.To assess the proportion of EBPT utilization in septic patients, according to the presence/absence of AKI.To describe indication, modality, and duration of EBPT in septic patients, also according to the presence/absence of AKI.\To assess proportion, indication, modality, and duration of SETS in septic patients with renal failure.To assess association between SETS utilization and 90-day mortality in septic patients with renal failure.To describe changes in blood lactate, vasoactive inotropic score (VIS), Sequential Organ Failure Assessment (SOFA) score, and AKI staged (with KDIGO criteria) before and after starting EBPT and SETS.To evaluate relationship between 90-day mortality and changes in blood lactate, VIS, SOFA score, and AKI staged (with KDIGO criteria) in patients undergoing EBPT and SETS.To evaluate relationship between fluid accumulation at EBPT initiation and 90-day mortality.To assess the frailty score change at 28- and 90-day post-discharge.To identify possible risk factors (e.g., baseline clinical parameters, features of EBPT) for 90-day mortality in patients with EBPT or SETS.To investigate the impact of time of EBPT and SETS on renal outcomes, mortality, ICU and hospital length of stay, and 28-day free EBPT (free-SETS days).

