### Statistical analysis

#### Sample size

This is a cohort study aimed at determining the cumulative incidence (absolute risk) of EBPT use in septic shock patients. Since no data are available in the literature, we employed a conservative estimate of 50% as the proportion for EBPT utilization in septic shock patients in the ICU to estimate the study sample size. According to Cochran’s formula, we estimated a sample size of at least 97 patients for estimating EBPT utilization with a 95% confidence level and 10% relative precision. If the number of participating centers is sufficient, the study will enroll a maximum of 385 patients to increase accuracy to within 5%.

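### The objective on time of EBPT/SETS leaves 'time' undefined and pairs it with outcomes that overlap it: stay from admission with delay or duration, and free days with duration

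*Protocol article*

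**What the plan says.** Under Secondary outcome, the last objective of the protocol article is "To investigate the impact of time of EBPT and SETS on renal outcomes, mortality, ICU and hospital length of stay, and 28-day free EBPT", with the SETS equivalent added. The exposure is given only as time; the article does not say whether this is the delay from ICU admission to treatment start or the length of treatment. The Data collection section lists timing and duration as separate items for both EBPT and SETS, so either reading is possible.

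The Statistical analysis plan section states: "Multivariable generalized linear regression models will be performed to investigate the association between clinical outcomes", and the outcomes and patients are "renal outcomes, mortality, ICU and hospital length of stay, free days from EBPT or SETS) and demographic/clinical variables in patients undergoing EBPT or SETS". It adds: "Relationships will also be analyzed using survival analysis (Kaplan–Meier approach and Cox proportional hazard models) to account for failure time and censoring data". The test level is fixed by "All hypothesis tests will be two-sided, and *P* < 0.05 will be considered to indicate statistical significance".

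On the clock, the Setting section says: "Patient enrollment will coincide with ICU admission, and monitoring along with data recording will continue until hospital discharge". No other time origin is given for length of stay or for the 28-day window. No landmark, delayed entry or time-dependent treatment is mentioned.

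**The concern.** A patient is in the treated group only if still in the ICU when treatment starts. A patient started on day 5 has already stayed 5 days; one started on day 1 may leave on day 2. In an analysis restricted to treated patients, stay from admission therefore has a floor equal to the delay, and a regression of stay on delay tends to slope upward whatever treatment timing does. If duration is the exposure, treatment days are part of the stay and are exactly the days subtracted to obtain EBPT-free days. Covariate adjustment does not remove an overlap of this kind.

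The Background section names timing and duration of these therapies as unresolved, and the Discussion says the results should guide treatment decisions. A built-in finding that earlier start shortens stay, or that shorter treatment gives more free days, could be reported as significant and read as such guidance.

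**Working it through.** **Inputs from the article.** Two-sided 0.05; 50% EBPT use ("we employed a conservative estimate of 50% as the proportion for EBPT utilization"); 97 patients at minimum and 385 at maximum. Those sample sizes reproduce as 1.96² × 0.25 / 0.10² = 96.04, so 97, and 1.96² × 0.25 / 0.05² = 384.16, so 385, with precision in absolute percentage points. Treated patients are then 0.5 × 97 = 48.5 (about 49) or 0.5 × 385 = 192.5 (192 or 193). The article gives no figure for the timing objective itself.

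**Assumptions, not in the documents.** Mean delay of 1, 2 or 3 days (exponential), and the stay distributions stated below. Timing has no effect in any scenario.

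**1. Delay and stay, with stay after initiation unrelated to delay.** Stay = delay + remaining stay, so the slope of stay on delay is 1.0. Take remaining stay as gamma with shape 2 and mean 10 days, SD 5 × √2 = 7.07. The correlation is m / √(m² + 50), where m is the mean delay:
- m = 1: 1 / √51 = 0.14
- m = 2: 2 / √54 = 0.27
- m = 3: 3 / √59 = 0.39

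At 192 treated, 0.14 × √192 = 1.94 against a critical value of 1.96, so about half of studies reject falsely. Simulation gives 50%, 96% and about 100%. At 49 treated it gives about 15–18%, 44–46% and 78%, the spread being between simulation runs. With a different split (exponential delay, duration of mean 3 days and later stay of mean 8 days) the figures are 35% to 99.5% at 193 and 13% to 64% at 49.

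**2. Delay and stay, with total stay unrelated to delay.** Total stay is gamma with mean 12 days (shape 2 or 4), and a patient is treated only if the delay is shorter than the stay. The floor alone produces false slopes of about 0.1 to 0.6 per day and 6–69% rejection at 192 treated, and less at 49.

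**3. Duration and stay.** With the exponential split above, the correlation is 3 / √(m² + 9 + 64), which is 0.35 at m = 1 and 0.33 at m = 3. False rejection is 65–69% at 49 treated and over 99% at 193.

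**4. Duration and free days.** In a survivor whose treatment lies within the 28 days, free days = 28 − duration, so r is −1.00. If deaths score zero (40% deaths assumed), r is −0.14, with rejection of 12–14% at 49 and about 52% at 193.

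**5. Delay and free days.** In survivors the delay cancels: free days depend on how many days were treated, not when. Rejection is 4–6%, as it should be. A link appears only through deaths, if free days are counted as days alive and free with no penalty: with 40% deaths the slope is about +0.4 per day of delay, and rejection is 6–37% at 193. The article does not say how deaths are scored.

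**6. Candidate remedies for delay.** Counting stay from treatment start restores 4–6% rejection in scenario 1. In scenario 2 it errs the other way: slope −0.4 to −0.9, with 16–96% rejection at 192. A delayed-entry model on the admission clock gives 5–8% in scenario 2. It is not neutral in every scenario either. In scenario 1 the discharge hazard rises with time since treatment start, so on a given day since admission a later starter has the lower hazard.

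**The case against.** **The article is condensed.** Origins of length of stay and of the 28-day window are the kind of detail left to a full protocol or analysis plan, and neither is shown. This stands, and the absence of those definitions is not itself the point. The point is the stated pairing of exposure with outcomes, and a stated model class that does not handle the pairing.

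**The regression sentence does not name delay or duration as predictors.** It refers only to demographic and clinical variables. That is correct, but its outcome list matches that of the objective and its analysis set is the treated patients, so it is the evident analysis for this objective. The survival sentence is general and does not rescue it: a Cox model from admission in treated patients, with delay as a fixed covariate, has the same floor.

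**The size is uncertain.** This stands in full. The larger figures need the maximum sample, which depends on having enough centres; the 50% use is a planning placeholder; and the delays and stays are assumed. Independence of remaining stay and delay is only one version of no effect. The other version gives a weaker artefact, barely above nominal at its lower end.

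**A reader might infer that the whole objective is unanswerable, or that delay and duration are each built into every outcome.** The documents support neither. Mortality and renal outcomes are in the same objective and contain no such component, and delay has no built-in link with free days in survivors.

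**Counting stay from treatment start is not a clean repair.** This also stands; it can reverse the bias, and it is given a secondary place in the fix.

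**Conclusion.** The defect is real but limited to three pairings: delay with stay from ICU admission, duration with stay, and duration with EBPT/SETS-free days. For the first, the direction under no effect is upward. Its size rests on assumptions outside the documents: at about 192 treated and mean delays of 1 to 3 days, 6–69% false rejection if total stay is unrelated to delay and 50–100% if stay after initiation is, with lower figures at about 49 treated. Duration with stay was examined in one scenario only, where the overlap is substantial at either sample size. Duration with free days is circular in survivors and is diluted only by the scoring of deaths. The issue sits in one secondary objective; the primary outcome, the proportion receiving EBPT, is untouched. It is worth correcting because the artefact could pass for evidence on timing.

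**What to change.** - State whether time means delay to start or duration. If both are wanted, write two objectives.
- For delay, replace the generalized linear model of total stay with a time-to-discharge model on the ICU-admission clock. Patients enter the risk set at EBPT/SETS start (or treatment is time-dependent), death is a competing event, and severity at initiation (SOFA, lactate, VIS) enters as covariates.
- Report stay after initiation only as a sensitivity analysis, and say that it can be biased in the opposite direction. The two clocks embody different meanings of no effect, so a conclusion that appears on only one of them should be presented with that caution.
- Where duration is the exposure, do not use free days or total stay as outcomes; report duration descriptively.
- State how deaths count in free days.

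**Cost.** A change of wording to one objective and its analysis, some additional modelling, and a summary less familiar than mean total stay. Timing and duration of treatment are already collected; confirm that the severity measures are also recorded at treatment start.
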